| 
1. Compare the impact of the online vestibular rehabilitation tool with standard written instructions after acute onset vertigo on different aspects of everyday living (superiority).
 
2. Compare how the online vestibular rehabilitation tool influences the walking ability and standing balance compared with standard written instructions after acute onset vertigo (superiority).
 
3. Compare how the online vestibular rehabilitation tool influences the lateral canal vestibulo-ocular reflex (VOR) recovery compared with standard written instructions after acute onset vertigo (superiority).
 
4. Compare the long-term effects of early vs. delayed online vestibular rehabilitation on vestibular symptoms and mobility (superiority).
 
5. Compare the effects of online vestibular rehabilitation with standard written instructions on vestibular rehabilitation compliance (superiority).
 
6. Compare the health economic effects of online vestibular rehabilitation with standard written instructions (superiority).
 
7. Compare the kinematic output data from a portable multi-sensor movement analysis system, with the kinematic output data received from the mobile phone app (comparative and partly superiority).
 | 
1. The between groups mean dizziness handicap inventory (DHI) score at 6 weeks and 3 months after vertigo onset.
 
2. The between groups changes in timed 25-foot walk test (T25-FW) from baseline to 6 weeks and 3 months; the between groups body sway during standing and walking; and the mobility at 6 weeks and 3 months after vertigo onset.
 
3. The between groups changes in video head impulse test (vHIT, site-dependent) measured lateral canal VOR gain and saccades from baseline at 6 weeks and 3 months after vertigo onset.
 
4. The between groups mean vertigo symptom scale short form (VSS-SF) score at 12 months after vertigo onset; and the between group pedometer-derived number of steps walked since last visit at 6 weeks and 3 months after vertigo onset.
 
5. The between groups mean number of weekly training sessions at 6 weeks.
 
6. Health economic effects on all levels of care (primary, specialized) and society (sick leave).
 
7. The added-value from using a multi-sensor movement analysis system to receive multi-joint kinematic output, in comparison to using a mobile phone placed on the hip to receive center-of-mass kinematic output.
 |

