Basic body sway data will be collected by each site study coordinator using a locally developed application which utilizes cell phone built-in motion tracking. An enhanced gait analysis with a wearable motion tracking system will be performed at Umeå University Hospital for in-depth measurements.

The participants will be instructed to keep a provided pedometer on them as often as possible during the first 3 months. The total number of steps for the first 6 weeks, and from week 6 to 3 months will be recorded into REDCap will be compared between the study arms at week 6 and after 3 months.

At sites with access to vHIT we will also measure VOR gain and catch-up saccades by performing vHIT at day 0, 6 weeks and 3 months.

The catch-up saccades (yes/no, proportion of impulses with saccades) will also be compared between the study arms at 6 weeks and 3 months (affected side).

The 12 months data collection to capture potential long-term effects of early intervention will be performed by the Umeå University Hospital study coordinator by contacting all participants by telephone at 12 months after inclusion. During this phone call one last round of VSS-SF questionnaire data will be collected (Figure 1).

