**Table 1. Schedule of events**

| Visit/contact                       | Baseline | 3 weeks
(by phone) | 6 weeks | 3 months | 12 months (by
phone) | Comments                                            |
|-------------------------------------|----------|-----------------------|---------|----------|-------------------------|-----------------------------------------------------|
| Target day                          | 0        | 21 +/-3               | 42 +/-3 | 90 +/-7  | 360 +/-14               |                                                     |
| Eligibility
screening, history   | x        |                       |         |          |                         |                                                     |
| Randomization                       | x        |                       |         |          |                         |                                                     |
| VSS-SF                              | x        | x                     | x       | x        | x                       | Primary endpoint @6
weeks                        |
| EQ-5D                               | x        |                       | x       | x        | x                       |                                                     |
| DHI                                 | x        |                       | x       | x        |                         |                                                     |
| T25-FW                              | x        |                       | x       | x        |                         |                                                     |
| Body sway                           | x        |                       | x       | x        |                         |                                                     |
| Enhanced body
sway analyses      | x        |                       | x       | x        |                         | At selected sites only                              |
| vHIT                                | x        |                       | x       | x        |                         | At selected sites only                              |
| Steps, falls and
fractures       |          |                       | x       | x        |                         | Total steps, since
enrollment or last visit      |
| BPPV questions                      |          |                       | x       | x        |                         |                                                     |

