**Table 2. Aim-specific statistical analysis plan**

| Analysis                                                                        | Subjects analyzed                         | Sample size (15% attrition is expected in power calc.) | Estimated difference based on previous results mean (SD) | Power   | Method                     |
|---------------------------------------------------------------------------------|-------------------------------------------|--------------------------------------------------------|----------------------------------------------------------|---------|----------------------------|
| Between group mean VSS-SF difference @w3, @w6, @m3, @m12                        | All participants                          | 92+92                                                  | 8.1 (7.4) vs 11.5 (9.9)                     | 90%     | ANCOVA                     |
| Between group mean EQ-5D difference until m3                                    | All participants                          | 92+92                                                  | Unknown                                                  | Unknown | Mixed models               |
| Between group mean EQ-5D difference @12m                                        | All participants                          | 92+92                                                  | Unknown                                                  | Unknown | ANCOVA                     |
| Between group mean DHI difference until m3                                      | All participants                          | 92+92                                                  | 24.4 (20.8) vs 29.2 (21.1)                  | 68%     | Mixed models               |
| Mean of means T25-FW (seconds) and timed balance tests (seconds) until m3       | All participants                          | 92+92                                                  | Unknown                                                  | Unknown | Mixed models               |
| Between group mean difference of means of vHIT gain (affected side) @w6 and @m3 | Participants at sites with access to vHIT | 50+50                                                  | 0.52 (0.24) vs 0.69 (0.25) *31                | 99%     | Ranked ANCOVA              |

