| Proportion with catch-up saccades                                               | Participants at sites with access to vHIT | 50+50                                                  | Unknown                                                  | Unknown | Binary logistic regression |

|                                                                                                |                        |       |                         |         |                            |
|------------------------------------------------------------------------------------------------|------------------------|-------|-------------------------|---------|----------------------------|
| on vHIT (affected side) @w6 and @m3                                                            |                        |       |                         |         |                            |
| Body sway until m3                                                                             | All participants       | 92+92 | Unknown                 | Unknown | Mixed models               |
| Enhanced body sway analysis (gait analysis) until m3                                           | Umeå participants only | 25+25 | Unknown                 | Unknown | Mixed models               |
| Total steps since last visit @w6 and @m3.                                                      | All participants       | 92+92 | Unknown                 | Unknown | ANCOVA                     |
| Self-reported vestibular rehabilitation compliance until 6w (mean number of training sessions) | All participants       | 92+92 | Unknown                 | Unknown | Mixed models               |
| Proportion with falls or fractures                                                             | All participants       | 92+92 | Unknown                 | Unknown | Binary logistic regression |
| Proportion with BPPV                                                                           | All participants       | 184   | Estimated frequency 10% | N/A     | Binary logistic regression |

Abbreviations: VSS-SF = vertigo symptom scale short form; EQ-5D = EuroQol five-dimension scale; DHI = dizziness handicap inventory; T25-FW = timed 25-foot walk test; SD = standard deviation; vHIT = video head impulse test; @w6 = at 6 weeks; @m3 = at 3 months; @m12 = at 12 months.

\*Power calculations based on mean gain differences before and after vestibular rehabilitation

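### Pedometer activity is compared as raw total steps per period although the visit windows let the periods differ in length, and the protocol conflicts on a missed 6-week visit

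*Protocol*

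**What the plan says.** Secondary endpoint 4 (synopsis and section 5.2) includes the "pedometer-derived number of steps walked since last visit at 6 weeks and 3 months after vertigo onset". Section 6.7 describes the variable as two period totals: "The total number of steps for the first 6 weeks, and from week 6 to 3 months will be recorded into REDCap". In Table 1 the comment on the steps row starts the count from "enrollment or last visit". Table 2 lists "Total steps since last visit @w6 and @m3", analysed by ANCOVA in all participants (92+92), with expected difference and power both unknown.

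None of these places divides the count by days. The adjustment variables in section 9.3 are the baseline value of the outcome, sex, age, education, number of chronic diseases and AVS etiology; interval length is not among them. Table 1 schedules no baseline step count, so baseline adjustment cannot absorb the differences either.

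Table 1 puts the 6-week contact at day 42 +/-3 and the 3-month visit at day 90 +/-7. On wear, section 6.7 asks participants to "keep a provided pedometer on them as often as possible during the first 3 months". The only missing-data rule (section 9.9) covers the primary VSS-SF endpoint.

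**The concern.** A step total is daily walking multiplied by the days counted. When the days vary between participants for scheduling reasons, the outcome measures interval length as well as mobility. The protocol already uses a rate where exposure matters: training compliance is a mean number of weekly sessions. Steps are treated differently.

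At stake are the precision and the meaning of the only activity measure in endpoint 4, which is reused in endpoint 9 to compare participants with and without BPPV. There is also a gap at the 6-week contact. The primary VSS-SF is taken by telephone, so a participant could miss the site visit, still supply the primary endpoint and return at 3 months. The protocol's wordings then lead to different 3-month step values for that person.

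**Working it through.** The protocol gives no difference, SD or power for steps, so there is no stated figure to reproduce. The check is day-count arithmetic from Table 1, followed by a variance calculation under stated assumptions.

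**1. Length of the counting periods**
- Week-6 day: 42 - 3 = 39 to 42 + 3 = 45.
- Month-3 day: 90 - 7 = 83 to 90 + 7 = 97.
- First period: 39 to 45 days; 45/39 = 1.15.
- Second period: shortest 83 - 45 = 38, nominal 90 - 42 = 48, longest 97 - 39 = 58; 58/38 = 1.53.

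At constant daily walking the recorded total is proportional to these days. On a steps-per-day scale every ratio is 1.00.

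**2. Added variance with in-window visits**

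Assumptions: visit days uniform over the whole days in each window; daily steps independent of interval length; between-person CV of daily steps (CVd) 0.4, 0.5 or 0.6. The protocol gives none of these.

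For total = daily steps x days, with CVt the CV of interval length:

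variance ratio (squared CV of total / squared CV of daily steps) = 1 + CVt² + CVt²/CVd²

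- First period: variance of days = (7² - 1)/12 = 4, mean 42, CVt² = 4/1764 = 0.0023.
- Second period: variance of days = 4 + (15² - 1)/12 = 4 + 18.67 = 22.67, mean 48, CVt² = 22.67/2304 = 0.0098.

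| CVd | First period | Second period |
|---|---|---|
| 0.4 | 1.016 | 1.071 |
| 0.5 | 1.011 | 1.049 |
| 0.6 | 1.009 | 1.037 |

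The inflation is therefore about 1-2% at week 6 and 4-7% at month 3. For scale, the month-3 figures correspond to 92/1.071 = 86 to 92/1.037 = 89 effective participants per arm instead of 92.

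**3. Missed 6-week visit**

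- If the count runs from the last visit (section 5.2, Table 1, Table 2) and that means the last visit attended, the month-3 total covers 83 to 97 days. Against the nominal 48: 83/48 = 1.73, 90/48 = 1.88, 97/48 = 2.02.
- If the count runs from week 6 (section 6.7), there is no starting reading. The value is missing unless the pedometer stores dated counts, which the protocol does not say.

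**4. What a missed visit could do to an arm mean (illustration only)**

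Under the first reading, if a share f of an arm misses week 6 but attends month 3, the arm mean is multiplied by 1 + f x (1.875 - 1).

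- f = 5%: 1.044. f = 10%: 1.088. f = 15%: 1.131.
- Between-arm ratio with identical walking: 10% against 5%, 1.0875/1.04375 = 1.04; 15% against 5%, 1.13125/1.04375 = 1.08; 15% against 0%, 1.13. Equal shares give 1.00.

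**The case against.** A reader might infer that the choice of a raw total can change the trial's steps result two-fold. The documents do not support that. The factor of about two belongs to one participant's recorded month-3 total, after a missed 6-week visit, and only under the count-from-last-visit wording. The wider extreme, 97/38 = 2.55, sets such a person against the shortest in-window interval and is likewise a comparison of two individuals. The arm comparison moves far less, and its expected ratio stays at 1.00 when timing and attendance are alike in the arms.

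A reader might also take much larger variance inflation as established. If 10% missed week 6 and their long counts were used, the CV of interval length would rise to about 0.26 and the variance ratio to between 1.25 (CVd 0.6) and 1.48 (CVd 0.4). But the protocol gives no rate of participants who miss week 6 and return at month 3. Its stated rate ("15% attrition is expected in power calc") concerns drop-out, and people who drop out supply no month-3 total. Nor does open allocation show that visit timing differs by arm: both arms follow the same schedule.

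Other fair points: steps are part of one of nine secondary endpoints, the pass criterion rests on VSS-SF alone, and walking and balance are also measured by the timed walk and body sway. An analysis plan that is not shown might convert totals to rates. That last point does not remove the concern, because the protocol does not leave the scale open: it fixes an undivided total and names the analysis method.

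**Conclusion.** The point holds as a loss of precision and an inconsistency in a secondary endpoint. In-window scheduling alone makes recorded totals for identical walking differ by up to 1.15 (first period) and 1.53 (second). Under the stated assumptions, the variance rises by about 1-2% at week 6 and 4-7% at month 3. Bias between arms arises only if visit timing or missed visits differ by arm, which the protocol neither shows nor rules out.

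Separately, the wordings disagree on a missed 6-week visit: a total of about 1.7 to 2.0 times the nominal length, or no value. The day counts come from Table 1; the uniform visit days and the CV range are assumptions. The primary endpoint and the pass criterion are not affected.

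**What to change.** Define the outcome as mean steps per day in each period: the count divided by the days between the actual start and reading dates. First confirm that these dates are recorded; the protocol does not say so expressly, and an eCRF time stamp shows when data were entered, not when the pedometer was read.

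State that a cumulative 0-3 month count is not used as the week-6-to-month-3 value. Where the 6-week reading is absent, it may be reported as steps per day over the whole 0-3 month period. Align endpoint 4 (synopsis and section 5.2), section 6.7, Table 1 and Table 2.

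The cost is a few lines of wording and no new outcome measurement, provided the dates exist. One limit remains and should be acknowledged: dividing by calendar days does not correct for days on which the pedometer was not worn. The protocol sets no minimum wear and does not say that wear days are recorded, so steps per day would still mix walking with wear.

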**Table 1. Schedule of events**

| Visit/contact                       | Baseline | 3 weeks
(by phone) | 6 weeks | 3 months | 12 months (by
phone) | Comments                                            |
|-------------------------------------|----------|-----------------------|---------|----------|-------------------------|-----------------------------------------------------|
| Target day                          | 0        | 21 +/-3               | 42 +/-3 | 90 +/-7  | 360 +/-14               |                                                     |
| Eligibility
screening, history   | x        |                       |         |          |                         |                                                     |
| Randomization                       | x        |                       |         |          |                         |                                                     |
| VSS-SF                              | x        | x                     | x       | x        | x                       | Primary endpoint @6
weeks                        |
| EQ-5D                               | x        |                       | x       | x        | x                       |                                                     |
| DHI                                 | x        |                       | x       | x        |                         |                                                     |
| T25-FW                              | x        |                       | x       | x        |                         |                                                     |
| Body sway                           | x        |                       | x       | x        |                         |                                                     |
| Enhanced body
sway analyses      | x        |                       | x       | x        |                         | At selected sites only                              |
| vHIT                                | x        |                       | x       | x        |                         | At selected sites only                              |
| Steps, falls and
fractures       |          |                       | x       | x        |                         | Total steps, since
enrollment or last visit      |
| BPPV questions                      |          |                       | x       | x        |                         |                                                     |
| BPPV testing                        |          |                       |         | x        |                         |                                                     |
| Compliance                          |          | x                     | x       |          |                         | Questionnaire data,
number of weekly
sessions |
| Trial termination
form (local)   |          |                       |         | x        |                         | Last site visit @ 3
months                       |
| Trial termination
form (central) |          |                       |         |          | x                       |                                                     |
| Estimated time
requirement       | 150 min  | 15 min                | 120 min | 120 min  | 15 min                  | Total 7 hours per
participant                    |

Abbreviations: VSS-SF = vertigo symptom scale short form; EQ-5D = EuroQol five-dimension scale; DHI = dizziness handicap inventory; T25-FW = timed 25-foot walk test; SD = standard deviation; vHIT = video head impulse test.

## 6.8. Monitoring plan

The study will be monitored by an independent monitor before the study begins, during the study conduct, and after the study has been completed, to ensure that the study is carried out according to the CIP and that data is collected, documented, and reported according to ISO 14155:2020 and applicable ethical and regulatory requirements. Monitoring is performed as per the study's monitoring plan and is intended to ensure that the subject's rights, safety, and well-being are met as well as data in the eCRF are complete, correct, and consistent with the source data.

Monitoring will be performed by visits on site or by telephone call or video contact visits using a secure platform with encrypted communication.

Details of the monitoring activities are outlined in a separate risk-based monitoring plan.

## 7. Informed consent process

### 7.1. General process for informed consent

Designated personnel at care units (emergency departments, medical/neurological departments, ear-nose-throat departments/clinics and health centers) briefly inform potential subjects about the study and ask if they are interested and approve of receiving a call to book a visit for more information and written information about the study.

The local study coordinator calls/meets those who are interested and inform about the study and books an inclusion visit.

The principal investigator or delegated members of the study team at each site shall ensure that the subject is given full and adequate oral and written information about the study, its purpose, any risks and benefits as well as inclusion and exclusion criteria. Subjects must also be informed that they are free to discontinue their participation in the study at any time without having to provide a reason. Subjects should be given the opportunity to ask questions and be allowed time to consider the provided information and participation in the clinical investigation. If the person chooses to participate, both the subject and the member of the study team shall sign the informed consent form. A copy of the subject information as well as a copy of the informed consent form shall be provided to the subject. The subject's signed and dated informed consent must be obtained before performing any study-specific activity in the study. The process shall be documented in the subject's source documents and the signed informed consents shall be maintained with the essential documents. If new information becomes available that can significantly affect a subject's future health and medical care, that information shall be provided to the affected subject(s) in written form. If new information is added to the study, the subject has the right to reconsider whether he/she will continue their participation.

